### Objectives

The objectives are as follows: to investigate in a randomized controlled parallel-group trial whether (1) daily smartphone-based outpatient monitoring and treatment *including* clinical feedback versus (2) daily smartphone-based monitoring *without* clinical feedback or (3) daily smartphone-based mood monitoring *only* improves mood instability in patients with bipolar disorder and, furthermore, to investigate if daily smartphone-based monitoring, *including* clinical feedback, improves *questionnaire-based* quality of life, self-rated depressive symptoms, self-rated manic symptoms, perceived stress, and satisfaction with care, as well as *register-based* risk of psychiatric hospitalization and cumulated days of psychiatric admission as compared with daily smartphone-based monitoring *without* clinical feedback and daily smartphone-based mood monitoring *only* in patients with bipolar disorder. In addition, this is to investigate if daily smartphone-based monitoring, *including* clinical feedback, improves *smartphone-based* measures of stress, anxiety, irritability, activity, sleep duration, days with adherence to medication, days without mixed mood, and adherence to smartphone-based monitoring as compared with daily smartphone-based monitoring *without* clinical feedback in patients with bipolar disorder.

## Methods

The present trial protocol is reported according to the CONsolidated Standards Of Reporting Trials (CONSORT) statement and Standard Protocol Items: Recommendations for Interventional Trials (SPIRIT) [36–38] (Table 1 and Additional file 1).

**Table 1 Tab1:** Schedule of enrolment, interventions, and assessments in the SmartBipolar randomized controlled trial according to the SPIRIT checklist

Study period		
	**Baseline**	**Post allocation**
**TIMEPOINT**	0 months	6 months
**Enrollment**		
Informed consent	X	
Allocation	X	
**Interventions**		
Daily smartphone-based monitoring and treatment *with* clinical feedback loop	X	X
Daily smartphone-based monitoring and treatment *without* clinical feedback loop	X	X
Daily smartphone-based mood monitoring only	X	X
**Assessments**		
Smartphone-based mood monitoring	Daily during the entire follow-up period	
Questionnaires^a^	X	X
Registry data^b^		X

^a^Quality of life according to WHO Quality of Life-BREF (WHOQOL-BREF); Self-rated depressive symptoms according to Major Depressive Inventory (MDI); Self-rated manic symptoms according to Altman Self Rating scale for Mania (ASRM); Perceived stress according to Cohen’s Perceived stress scale; Satisfaction with care according to Verona Satisfaction Scale-Affective Disorder (VSS-A)

^b^Number and duration of psychiatric hospitalization during follow-up, and use of medication during follow-up

The trial protocol describes a randomized controlled parallel-group superiority trial, the SmartBipolar trial, investigating the effect of smartphone-based monitoring and treatment in adult patients with bipolar disorder. The SmartBipolar trial is part of a larger CAG bipolar trial [20] and therefore has some of the same secondary and tertiary outcome measures.

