### Trial design and study organization

The SmartBipolar trial is designed as a pragmatic randomized controlled parallel-group trial with a balanced allocation ratio (1:1:1) of adult patients with bipolar disorder stratified according to psychiatric center from where the patients receive outpatient treatment as part of the CAG Bipolar specialized outpatient treatment (Psychiatric Center Copenhagen, Psychiatric Center North Zealand, Psychiatric Center Amager, Psychiatric Center Glostrup, Psychiatric Center Ballerup in the Capital Region of Denmark). The patients are randomized to the SmartBipolar trial during a 6-month trial period (see description of intervention below).

The included patients are randomized to either active use of the entire Monsenso system, including clinical feedback (the intervention group), or to the use of the entire Monsenso system without clinical feedback (control group 1) or to mood monitoring only (control group 2). Patients continue with treatment as usual during the trial period. The flow diagram of the SmartBipolar trial is presented in Fig. 1. The SmartBipolar trial is conducted at the psychiatric centers listed above. No changes in study design or methods have been made after trial commencement.

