### Participants and settings

All patients with a bipolar disorder diagnosis according to the International Classification of Diseases, version 10 (ICD-10), receiving treatment in the CAG Bipolar outpatient clinics in the Mental Health Services, Capital Region of Denmark, are invited to participate in the trial. The staff consists of specialists in psychiatry and psychologists, as well as nurses, social workers, and recovery mentors with a specific interest and clinical experience and knowledge about the diagnosis and treatment of bipolar disorder. The physicians follow evidence-based psychopharmacological treatment as according to established guidelines [39], and treatment also encompasses group-based psychoeducation, coordinated targets to improve quality of life by increasing concordance between clinicians, patients, and relatives as well as continued ongoing supervision by a specialized clinical team [20].

The inclusion criteria are as follows: patients over the age of 18 years with a bipolar disorder diagnosis according to the International Classification of Diseases, version 10 (ICD-10), who are receiving treatment in the CAG Bipolar outpatient clinics in the Mental Health Services, Capital Region of Denmark, are eligible for inclusion. Thus, the patients are not newly diagnosed but receiving treatment for bipolar disorder during a more progressed state. Inclusion started in March 2021. The exclusion criteria are as follows: patients who do not own and use a smartphone and who lack Danish language skills are excluded. Patients meeting the inclusion criteria and having none of the exclusion criteria are invited to be enrolled in the SmartBipolar trial.

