### Study procedure

All potential patients are invited to participate in the SmartBipolar trial by the staff from the CAG Bipolar outpatient clinics the Mental Health Services, Capital Region of Denmark. Since patients are recruited from the CAG bipolar clinics, all patients are diagnosed with bipolar disorder according to ICD-10 by highly trained clinicians with a specific expertise within bipolar disorder. Patients who accept to participate in the SmartBipolar trial are screened by trained clinicians to make sure they fulfil the criteria for participation. Following inclusion, the included patients are randomized separately according to psychiatric center (Psychiatric Center Copenhagen, Psychiatric Center North Zealand, Psychiatric Center Amager, Psychiatric Center Glostrup, Psychiatric Center Ballerup) to either the intervention group or one of the two control groups for a six-month trial period.

An overview of the data collection during the trial is presented in Table 1. Information regarding psychiatric hospitalization and duration of admissions, and the use of medication, will be obtained after completion of the RCT by linkage of the unique personal identification number (CPR), which is assigned to all 5.9 million persons living in Denmark with the Danish Psychiatric Central Register [40].

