#### Secondary outcomes

Patient-based questionnaires collected at baseline and after six months using the following questionnaires: quality of life according to WHO Quality of Life-BREF (WHOQoL) [42]; self-rated depressive according to the Major Depressive Inventory (MDI) [43]; self-rated manic symptoms according to the Altman Self-rating Scale for Mania [44]; perceived stress according to Cohen’s Perceived stress scale (PSS) [45]; satisfaction with care according to scores on the Verona Satisfaction Scale-Affective Disorder (VSS-A) [46]. The validity of each questionnaire is available from the references. Patients will be contacted by the study nurse in case on non-response of the questionnaires. Furthermore, we will collect information on adherence to the Danish national guidelines of medical treatment of bipolar disorder according to use of the three main maintenance mood stabilizers for bipolar disorder: lithium, lamotrigine or quetiapine [39]. Risk of psychiatric hospitalization and cumulated number and duration of psychiatric hospitalization according to data from the population-based Danish Psychiatric Central Research Register [40].

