### Randomization

#### Sequence generation

The company randomize.net is used for the randomization (http://randomize.net). The randomization is conducted by the staff at each center using an online procedure with stratification according to the psychiatric center. Each center can log on to a webpage by using a secure code and will conduct the randomization on-site. Patients included in the trial are randomized with a balanced allocation ratio of 1:1:1 to (1) daily smartphone-based monitoring and treatment *including* a clinical feedback loop (intervention group) or (2) daily smartphone-based monitoring *without* a clinical feedback loop (control group) or (3) daily smartphone-based mood monitoring only (control group) (Table 1). Block sizes are (unavailable to those who enroll participants or assign interventions) used to help preserve unpredictability [49, 50]. The study uses a stratified design, where patients are stratified according to the CAG bipolar clinic.

The statistical analyses will be adjusted for the stratification variable and age and sex as possible prognostic variables. Furthermore, in analyses on continuous variables, potential differences in baseline scores on the outcome in question will be included as a potential confounder. If there is no statistically significant main effects of age and sex, these variables will be excluded from the final statistical analyses.

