### Statistical methods

Data from all randomized patients is collected until dropout or the end of the trial period. The analysis will be carried out with an intention-to-treat (ITT) approach. Concerning the primary, secondary, and tertiary outcomes, analyses will be done employing linear mixed-effects regression models with a random intercept for each participant. Differences in outcomes between the intervention group and the control groups will be analyzed, firstly in an unadjusted model (except for potential differences in baseline values of the outcome variable in analyses) and then in models adjusted for the stratification variable CAG bipolar clinic and for age and sex as possible prognostic variables. If there is no statistically significant main effects of age and sex, these variables will be excluded from the final analyses. Multiple regression models will be conducted investigating differences in the proportion of psychiatric hospitalizations and the cumulated duration of all psychiatric hospitalizations during the sex-month trial period. Models will be conducted as unadjusted and adjusted for CAG bipolar clinic (stratification variable), age, and sex. Missing data will be handled as missing at random.

For all statistical analyses, the statistical threshold for significance is *p* ≤ 0.05 (two-tailed). Data will be managed by [name] and [name] and entered using RedCap®. All analyses will be done using SPSS, version 22.0 (IBM, New York, NY, USA), and STATA version 13 (StataCorp LP, College Station, TX, USA).

Data about potential and enrolled participants will be stored in RedCap® and on secure servers at Monsenso during and after the trial. Data collected during the course of the trial will be kept strictly confidential and only accessed by members of the trial team. Participants be allocated an individual trial identification number. Participant’s details will be stored in a secure database. Only researcher from the trial team will access the data set. Potentially, we will share anonymized trial data with other researchers to enable international prospective meta-analyses. This will be applied for separately.

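### Register outcomes have no planned pre-randomisation value and the admission models omit history, which costs precision though not validity

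*Protocol article*

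**What the plan says.** In Table 1 of the protocol article the questionnaires are marked at baseline and at 6 months, while registry data are marked at 6 months only. Footnote b defines them as "Number and duration of psychiatric hospitalization during follow-up, and use of medication during follow-up". The medication outcome (Secondary outcomes) is adherence to the national guideline, judged by "use of the three main maintenance mood stabilizers for bipolar disorder: lithium, lamotrigine or quetiapine".

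On the population, Participants and settings states that "the patients are not newly diagnosed but receiving treatment for bipolar disorder during a more progressed state". It adds that "The physicians follow evidence-based psychopharmacological treatment as according to established guidelines", citing the same guideline reference that defines the medication outcome.

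On covariates, Statistical methods says of the hospitalisation analyses: "Models will be conducted as unadjusted and adjusted for CAG bipolar clinic (stratification variable), age, and sex". Sequence generation gives a general rule: "in analyses on continuous variables, potential differences in baseline scores on the outcome in question will be included as a potential confounder". Statistical methods also allows for baseline differences in the outcome in the mixed models.

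On the data source, Study procedure has admissions and medication obtained by one linkage on the personal identification number after the trial ends. It names only the national psychiatric register and states no look-back period.

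**The concern.** The protocol recognises that the earlier value of an outcome belongs in the model, but this cannot be carried out for the register outcomes as scheduled:

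- **Admission days** are continuous, so the baseline rule applies to them, but no register baseline is scheduled to feed it.
- **Admitted or not, and drug used or not,** are binary, so the rule in Sequence generation does not cover them. The mixed-model allowance in Statistical methods would meet the same lack of a register baseline.

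In patients already in treatment, whether a mood stabiliser is used in the six months after randomisation is likely to depend on whether it was used before. Earlier admissions may likewise predict later ones. If so, omitting the earlier value leaves explainable variation in the error term and leaves any chance difference between arms uncorrected.

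The medication result will be read closely, because the article reports increased lithium use in earlier trials of this system. The Discussion also claims sufficient power for secondary outcomes, without giving figures for the register outcomes.

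**Working it through.** The protocol states no design figure for the register outcomes, so there is none to reproduce.

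**Inputs.** From the protocol: 67 patients per arm, 1:1:1 randomisation stratified by centre, two-sided threshold 0.05 (Statistical methods). Assumed, because the documents give nothing: prevalence of prior use, persistence (the probability that a patient keeps the prior status) and the before-after correlation rho.

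**Step 1. Chance imbalance in prior use between two arms.** SD = sqrt(2p(1-p)/n).

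- p = 0.5: sqrt(2 x 0.5 x 0.5/67) = 0.086; 1.96 x SD = 0.169
- p = 0.8: sqrt(2 x 0.8 x 0.2/67) = 0.069; 1.96 x SD = 0.135

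This is 7 to 9 percentage points. It is zero in expectation and is already contained in the unadjusted standard error.

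**Step 2. How much passes into follow-up.** With p = 0.5, the before-after correlation is persistence minus (1 - persistence): 0.7 - 0.3 = 0.4, or 0.9 - 0.1 = 0.8. An imbalance of 8.6 points then carries over as 0.4 x 8.6 = 3.4 points or 0.8 x 8.6 = 6.9 points.

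**Step 3. Effect of adjustment on a persistent yes/no outcome.** 20,000 simulated two-arm trials per setting, 67 per arm, 50% prior use, linear adjustment for prior use, two-sided 0.05. The 10-point effect was added for prior users and non-users alike.

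| True difference | Persistence | Unadjusted mean | Unadjusted SD | Unadjusted rejection | Adjusted SD | Adjusted rejection |
|---|---|---|---|---|---|---|
| 0 | 0.7 | -0.001 | 0.086 | 4.5% | 0.079 | 4.9% |
| 0 | 0.9 | 0.000 | 0.086 | 4.6% | 0.052 | 5.0% |
| 0.10 | 0.7 | 0.102 | 0.086 | 21% | 0.079 | 25% |
| 0.10 | 0.9 | 0.100 | 0.086 | 21% | 0.051 | 52% |

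Check by formula: adjusted SD = unadjusted SD x sqrt(1 - rho^2). For rho 0.4 this is 0.0864 x sqrt(0.84) = 0.079. For rho 0.8 it is 0.0864 x sqrt(0.36) = 0.052.

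**Step 4. Continuous outcome (admission days).** Adjustment multiplies the variance of the contrast by about 1 - rho^2: 0.91, 0.75, 0.51 and 0.19 for rho = 0.3, 0.5, 0.7 and 0.9. The documents do not show where admission days fall in this range.

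**The case against.** A reader might infer that earlier prescribing and admissions are mixed into the arm contrast, so that the medication result would mainly show pre-trial treatment. The documents do not support this. Patients are randomised 1:1:1 within centre, so history is balanced in expectation. In the simulation the unadjusted contrast recovers the true difference and rejects a true null in 4.5% to 4.6% of trials. The 7 to 9 point imbalance is ordinary sampling error, not an extra error on top of it, and most of it passes into follow-up only when persistence is high. This objection stands in full.

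Further objections:

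- **The gain rests on assumptions.** This stands. At persistence 0.7 the gain is small (21% to 25%), and for admissions the documents offer no event rate at all.
- **History may be recorded elsewhere.** Assessments mentions baseline clinical data, and the ethics section says patient records are read to confirm clinical history. This stands in part: such data may exist, but the stated admission models do not use them.
- **Covariates for secondary outcomes are usual SAP content.** This would answer a silent protocol. Here the article states the covariate set and the register schedule, and together they leave its own baseline rule without a value to work on.
- **Earlier medication data may not be available from this linkage.** This stands as a caveat, since only the psychiatric register is named and no look-back is given.

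**Conclusion.** The point holds as one of precision on secondary outcomes. The register outcomes have no planned pre-randomisation value, the admission models omit history, and the baseline-adjustment rule cannot be applied to admission days and does not extend to the binary outcomes. Validity is not threatened: the planned contrasts are unbiased with type I error near 5%.

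For medication use, with 67 per arm and 50% prior use assumed, the omission costs between 4 and 31 percentage points of power for a 10-point difference (25 - 21 and 52 - 21), depending on persistence of 0.7 or 0.9. Prevalence and persistence are assumptions that the documents neither support nor contradict. For admissions the size cannot be fixed beyond the 1 - rho^2 range. The change is worth making because it is cheap and follows the protocol's own principle.

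**What to change.** Before the linkage is run, state in the protocol or SAP:

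1. A fixed pre-randomisation window, the same for every randomised patient, to be drawn in the same linked extraction for psychiatric admissions, admission days and use of the three mood stabilisers.
2. That each register outcome is adjusted for its own pre-randomisation value, binary as well as continuous, in addition to clinic, age and sex.
3. Which register supplies medication use and how far back it reaches. If earlier medication use proves unobtainable, say so and limit the adjustment to admissions.

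Keep the medication outcome as defined under Secondary outcomes. Recoding it as starting or stopping a mood stabiliser would change what is estimated, with 150 of 201 patients already included at the time of the article. Such a tabulation can be a descriptive supplement at most.

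Prespecification matters because researchers are aware of allocation outside data handling, and a history covariate chosen after the linkage would be less credible. The cost is a wider extraction range, possibly an extended data permission, and a few lines of text. No patient contact or extra visit is needed.

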### Trial design and study organization

The SmartBipolar trial is designed as a pragmatic randomized controlled parallel-group trial with a balanced allocation ratio (1:1:1) of adult patients with bipolar disorder stratified according to psychiatric center from where the patients receive outpatient treatment as part of the CAG Bipolar specialized outpatient treatment (Psychiatric Center Copenhagen, Psychiatric Center North Zealand, Psychiatric Center Amager, Psychiatric Center Glostrup, Psychiatric Center Ballerup in the Capital Region of Denmark). The patients are randomized to the SmartBipolar trial during a 6-month trial period (see description of intervention below).

The included patients are randomized to either active use of the entire Monsenso system, including clinical feedback (the intervention group), or to the use of the entire Monsenso system without clinical feedback (control group 1) or to mood monitoring only (control group 2). Patients continue with treatment as usual during the trial period. The flow diagram of the SmartBipolar trial is presented in Fig. 1. The SmartBipolar trial is conducted at the psychiatric centers listed above. No changes in study design or methods have been made after trial commencement.

**Fig. 1 Fig1:**
[figure not shown]
Flow diagram, the SmartBipolar randomized controlled trial

### Participants and settings

All patients with a bipolar disorder diagnosis according to the International Classification of Diseases, version 10 (ICD-10), receiving treatment in the CAG Bipolar outpatient clinics in the Mental Health Services, Capital Region of Denmark, are invited to participate in the trial. The staff consists of specialists in psychiatry and psychologists, as well as nurses, social workers, and recovery mentors with a specific interest and clinical experience and knowledge about the diagnosis and treatment of bipolar disorder. The physicians follow evidence-based psychopharmacological treatment as according to established guidelines [39], and treatment also encompasses group-based psychoeducation, coordinated targets to improve quality of life by increasing concordance between clinicians, patients, and relatives as well as continued ongoing supervision by a specialized clinical team [20].

The inclusion criteria are as follows: patients over the age of 18 years with a bipolar disorder diagnosis according to the International Classification of Diseases, version 10 (ICD-10), who are receiving treatment in the CAG Bipolar outpatient clinics in the Mental Health Services, Capital Region of Denmark, are eligible for inclusion. Thus, the patients are not newly diagnosed but receiving treatment for bipolar disorder during a more progressed state. Inclusion started in March 2021. The exclusion criteria are as follows: patients who do not own and use a smartphone and who lack Danish language skills are excluded. Patients meeting the inclusion criteria and having none of the exclusion criteria are invited to be enrolled in the SmartBipolar trial.

### Study procedure

All potential patients are invited to participate in the SmartBipolar trial by the staff from the CAG Bipolar outpatient clinics the Mental Health Services, Capital Region of Denmark. Since patients are recruited from the CAG bipolar clinics, all patients are diagnosed with bipolar disorder according to ICD-10 by highly trained clinicians with a specific expertise within bipolar disorder. Patients who accept to participate in the SmartBipolar trial are screened by trained clinicians to make sure they fulfil the criteria for participation. Following inclusion, the included patients are randomized separately according to psychiatric center (Psychiatric Center Copenhagen, Psychiatric Center North Zealand, Psychiatric Center Amager, Psychiatric Center Glostrup, Psychiatric Center Ballerup) to either the intervention group or one of the two control groups for a six-month trial period.

An overview of the data collection during the trial is presented in Table 1. Information regarding psychiatric hospitalization and duration of admissions, and the use of medication, will be obtained after completion of the RCT by linkage of the unique personal identification number (CPR), which is assigned to all 5.9 million persons living in Denmark with the Danish Psychiatric Central Register [40].

